### Eligibility Criteria

Eligibility criteria will be as follows: (1) aged 45 years or older, (2) living with osteoarthritis diagnosed by a health care professional, (3) living with cognitive concerns or dementia, (4) able to safely undertake study assessments and complete exercise without assistance, and (5) have appropriate medical clearance to take part. Exclusion criteria will be as follows: (1) MoCA score of less than 18; (2) unwilling or unable to provide written informed consent and comply with study requirements; (3) inability to speak and understand English unless a translator is available; and (4) contraindications to exercise in accordance with American College of Sports Medicine (ACSM) guidelines (Multimedia Appendix 2) [51], such as symptomatic hernias, proliferative retinopathy, uncontrolled arrhythmias, or rapidly progressing or terminal illness. Consent will be obtained by the lead researcher ([name]).

### Recruitment

A total of 20 participants with osteoarthritis and cognitive decline will be recruited through the UNSW Medicine and Health Lifestyle Clinic, StepUp for Dementia Research, and general practitioner and health district referrals. Study advertisements will also be displayed electronically via online social media platforms (eg, X, formerly known as Twitter [X Corp]; Facebook [Meta Platforms, Inc]; and LinkedIn [LinkedIn Corporation]). Initial contact will be made by potential participants emailing the study investigators through the study email or the StepUp team or by referral from a health professional. A member of the research team will then contact potential participants. Participants will be screened in person, online, or over the telephone to confirm their eligibility. The lead investigator will review participant screening data and confirm participant eligibility before providing the participant information sheet and consent form (Multimedia Appendix 3). If eligible and after written consent has been obtained, potential participants will be invited to an in-person screening visit. Demographic information, chronic disease history, lifestyle behaviors, and medication use will be documented. Potential participants will complete the Adult Pre-Exercise Screening System and Exercise and Sports Science Australia [42] screening questionnaires for exercise-induced symptoms (eg, chest pain and musculoskeletal pain; Multimedia Appendix 4). To ensure safety, only people cleared through the screening will be enrolled and randomized. Once deemed eligible, participants will complete written informed consent, and baseline testing will commence. Participants will be assigned a unique ID number to ensure personal details are not linked to collected data.

Due to ethical considerations where many potential participants may not be aware of cognitive decline, the term “thinking difficulties” will be used throughout study advertisements and participant information sheets. An ethically approved protocol is in place for advising people of their health assessment results (eg, cognition and depression) and referring them to their general practitioner where appropriate. Eligible participants will have mild cognitive impairment; therefore, they will have the capacity to provide informed consent.

Following successful screening, the participant will be allocated a unique ID number using the generated list. The RA who performs the randomization will advise the data collectors of the participants’ IDs by referring to the password-protected spreadsheet of participant names and allocated ID numbers. After completion of baseline testing, participants will be randomly assigned to the intervention (n=10) or waitlist control groups (n=10) using a computer-generated randomization list produced by a researcher external to the study group. In total, 20 participants will complete the program. After completing a 12-week period of usual care, those in the waitlist control group will then complete the 12-week HBMP. A 12-week follow-up will be performed to examine sustainability. Participants are allowed to withdraw from the trial at any time they wish and are assured that doing so would not alter their care or relationship with the university or the community clinic.

### Data Collection and Outcome Measures

#### Feasibility and Acceptability

The feasibility of the program will be determined by the number of eligible participants who provide consent and retention and adherence to the program (ie, number of exercise and education sessions attended, completed, and engaged with). Retention will be determined by the percentage of participants who provide consent and complete the program. Adherence will be determined by the percentage of program sessions attended by participants who enter the program. Adherence will be recorded using attendance records (recorded by the AEP and health psychologist facilitating the sessions). The acceptability of the program will be assessed by postprogram evaluation questionnaires after the program is completed.

#### Health Outcomes

Baseline and postintervention assessment visits will take between 90 and 120 minutes, including the health interview, physical assessment, and questionnaire completion. The RA completing assessments will be blinded to the condition (intervention or waitlist control groups). The RA will be trained and supervised by an AEP.

Secondary outcome measures will be completed before randomization at baseline and 12 weeks after intervention. The outcome measures (questionnaires outlined in the subsequent section) will be completed by an RA and a member of the research team who is blinded to the group allocation. Health outcome measures will include QoL (measured using the Short Form Health Survey-36) [46]; cognition (MoCA [36] and the Cambridge Neuropsychological Test Automated Battery attention, learning, and memory tasks); pain (Western Ontario and McMaster Universities Osteoarthritis Index) [44,52]; psychological health (Depression, Anxiety, and Stress Scale-21) [45]); and physical health (weight, waist circumference, blood pressure, functional fitness, strength, mobility, and balance). Balance exercises will be simple easy to perform movements that take place in a purposefully designed environment that minimizes the risk of falls (ie, they will be beside a wall, with an AEP closely monitoring them and simple exercises will be completed first, enabling the AEP to continually assess whether it is safe for the participant to continue to the slightly more challenging balance exercises).

The questionnaires (Table 1) will assess the participants’ health relevant to the outcome measures (eg, cognition, QoL, and psychological health). The data collection process will be administered using UNSW Qualtrics, except for the cognition measures, as these require the participant to draw on the printed tool (ie, pen and paper questionnaire). Participants will be asked questions by an experienced health psychologist and RA who has experience interviewing people with cognitive decline. They will enter the data directly onto a tablet or paper for the MoCA (with no identifying information, just a participant ID). The MoCA data will then be entered electronically. The health psychologist has received appropriate training to administer the MoCA [36] and a license (obtained in July 2022) and permission to train other staff and students to administer the tool. Participants will be invited to bring a support person with them if they wish, given that variability in level of independence is expected in this population (people with osteoarthritis and cognitive decline). All questionnaires have been validated and used extensively in the literature and with clinical populations, including people with osteoarthritis and cognitive decline.

### Data Management

The questionnaires will be completed within the UNSW Medicine and Health Lifestyle Clinic facilities. The data captured on Qualtrics and the Cambridge Neuropsychological Test Automated Battery software using a computer or tablet will be exported to Microsoft Excel and SPSS Statistics (IBM Corp) for data analysis and stored on a secure OneDrive (Microsoft Corporation) database hosted by UNSW, Sydney. The data will be entered, checked, and cleaned by 2 members of the research team. Only members of the research team will have access to the data. All recruited participants will be assigned a unique study ID number, ensuring no personal details, such as their names, are stored alongside data.

### Adverse Events

PA may cause concern in older adults and people living with chronic conditions. Adverse events may occur (eg, a fall), despite the safety protocols we have put in place (eg, AEP or RA closely monitoring participants during exercise in a purposefully designed clinic or laboratory setting with handrails). Throughout the trial and follow-up, adverse events will be documented, and risk will be continually assessed by appropriately trained professionals (ie, AEP). Reported adverse events will include details about the type of event, date, time, and duration; severity (mild to severe); whether it could have been avoided; outcome (solved to fatal); and whether it was related to the study (certainly, probably, possibly, unlikely, or cannot say). The relevant ethics committee and participant’s general practitioner will be informed about any serious event (eg, requiring hospitalization) that takes place during the study. Adverse events will be reported transparently alongside study outcomes. In accordance with the CONSORT (Consolidated Standards of Reporting Trials) statement [48] and similar to other studies [53], data from participants who are suspended from the trial due to an adverse event will be entered into the analysis by their allocated treatment group. The lead researcher will continue to communicate and support the participant and signpost them to relevant support services where appropriate. An independent safety monitoring process has been established (the data safety monitoring board) to oversee participant safety and review this trial. These arrangements have been documented in a safety monitoring plan, reviewed and approved by the human research ethics committee. All research staff involved in this trial have completed training and certification in Good Clinical Practice guidelines.

### Intervention

#### Overview

The HBMP has been designed in line with the strongest evidence for dementia risk reduction [20,21] and treatment for osteoarthritis [7,31,54]. Furthermore, the exercise component was designed according to international guidelines for prescribing exercise in older adults from the ACSM [51]. Health behavior theories that informed the intervention were the health belief model [55] and behavior change techniques [56]. The health belief model focuses on how individuals perceive health threats (eg, aging, pain, dementia, and decreased mobility) and the likelihood that actions taken toward their goals will lead to success. Behavior change techniques include shaping knowledge, providing information on the health consequences of behavior, action planning, self-monitoring of behavior, graded tasks, and social support. Participants will focus on goals, barriers, and enablers using the specific, measurable, achievable, relevant, and time-bound goals approach [57]. Taken together, the program aims to promote participants’ health behavior changes. Measures of behavior change, such as knowledge and self-efficacy, are not being included in this pilot feasibility trial, although following successful completion of the pilot, they will be incorporated into a fully powered RCT.

The program will be delivered within the UNSW Medicine and Health Lifestyle Clinic facilities by AEPs and health or clinical psychologists. The 12-week program sessions will take place twice per week (24 sessions in total) and will be 60 to 90 minutes long, including exercise, lifestyle, and behavior change education. Both weekly sessions will comprise 45 minutes of supervised exercise. The first weekly session will be followed by 45 minutes of education (including pain self-management, nutrition, sleep, and reducing smoking and alcohol consumption). Participants will be assigned to time slots suitable for them at the beginning of the program to help reduce the number of missed sessions. Catch-up sessions will be available for participants who are unable to attend their allocated slot. Four groups (2-8 participants per group) will complete the HBMP for 6 months (2 groups in a waitlist control group for the first 3 months). Participants can choose the days and times that suit them and will repeat those for the full 12-week program.

#### Exercise Component

The exercise component will be evidence based and delivered using a variety of exercise equipment available within the UNSW Medicine and Health Lifestyle Clinic facilities as well as through independent exercise sessions completed at home. Exercises will be modified for each individual based on ability and fitness. A combination of aerobic, resistance, balance, and flexibility exercises will be prescribed to suit the needs of the individual participants.

The ACSM guidelines state that older adults should aim to complete “resistance training twice a week and aerobic exercise of moderate intensity for 150-300 minutes a week, or vigorous intensity for 75-150 minutes per week” [51,58]. Therefore, the exercise prescription guidelines presented in Table 2 will be followed. Participants will complete resistance training twice weekly at the clinic in addition to 60 minutes of aerobic activity and 90 minutes or more of independent or home-based aerobic activity. Independent activity will be recorded each week on a printed record sheet and returned to the AEP upon completion. This will total the ACSM’s recommended 150 minutes per week of aerobic activity and 2 strength-based sessions that older adults should engage in for health benefits (Table 2) [51,58]. The prescriptive elements of all exercises performed will be recorded in program training sheets for each session to ensure all necessary details are captured. The education sessions will provide information on how participants can complete PA independently (Table 3).

**Table 2 table2:** Healthy Body and Mind Program—clinic-based exercise component.

	Aerobic exercise	Resistance exercise
Frequency	Twice weekly (clinic based)	Twice weekly (clinic based)
Duration	30 minutes	30 minutes
Intensity	Light to vigorous (light: RPE^a^ 8-10; moderate: RPE 11-13; vigorous: RPE 14-16) [59]	Light to vigorous (light: 30%-49% 1 RM^b^; RPE 9-11; moderate: 50%-69% 1 RM; RPE 12-13; vigorous: 70%-84% 1 RM; RPE 14-17)
Type	Major muscle groups: cycling (upright or recumbent), walking (treadmill), rowing, and stepping	Pin-loaded weight plate machines (eg, leg press, leg extension, leg curl, seated row, chest press, and latissimus [or “lat”] pull down), body weight, free weights, and resistance bands
Volume	Frequency×intensity×time	Sets×repetitions×days; 1 to 3 sets and 8 to 12 repetitions
Pattern	One continuous bout or multiple bouts (eg, 30 min or 3×10 min)	Rest between sets and exercises
Progression	Commence first exercise session in week 1 at low to moderate intensity (50%-60% HRmax^c^; RPE 9-13) and progress gradually as tolerated by the individual	Increased weights to ensure participants’ RPE remains within the required range

^a^RPE: rating of perceived exertion [59].

^b^RM: repetition maximum.

^c^HRmax: maximum heart rate (beats per min).

**Table 3 table3:** Healthy Body and Mind Program—lifestyle and behavior change education component in accordance with leading organizations.

Session topic^a^	Resource (fact sheets or guidelines) and organizations
Personalized goals and action plans	Behavior change techniques, action planning, and SMART^b^ goals
Nonpharmacological approaches	Osteoarthritis (Arthritis Australia); mild cognitive impairment (Dementia Australia)
Physical activity	Osteoarthritis fact sheet (Exercise is Medicine Australia); physical exercise and dementia (Dementia Australia)
Pain neuroscience education	UNSW^c^ Medicine and Health; Arthritis NSW^d^; Exercise is Medicine Australia; Musculoskeletal Australia
Nutrition	Healthy eating and arthritis (Arthritis Australia); food diary
Psychological health	Arthritis and emotional well-being (Arthritis Australia); depression and dementia fact sheet (Dementia Australia)
Social connections	Social connectedness in older adults (Centre for Healthy Brain Ageing, UNSW); American Association of Retired Persons
Sleep	Arthritis Foundation; Sleep Foundation; Musculoskeletal Australia
Alcohol and smoking	Arthritis Foundation; Australian Government Department of Health; American Heart Association
Participant’s choice	Participants allowed to choose areas they would like to focus on

^a^Each session was facilitated by educational slides developed by [name].

^b^SMART: specific, measurable, achievable, relevant, and time bound.

^c^UNSW: University of New South Wales.

^d^NSW: New South Wales.

The AEP and health psychologist will receive training from 2 of the study investigators ([name] and [name]) to deliver the exercise and education components. Exercise monitoring observations will take place to record and assess the participants’ compliance with the prescribed exercise program relevant to the secondary outcome measures. This data collection will be undertaken face-to-face during group exercise sessions. The AEP will conduct the clinical assessment and group exercise sessions. Each session’s data will be collected using program sheets already used in the clinic to capture descriptive details of specific exercises. Measurements of heart rate, blood pressure, and rating of perceived exertion (Borg Rating of Perceived Exertion [59]) will be recorded during the group sessions. These data will be analyzed to provide information on the overall intensity of exercise achieved in each group session.

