**Clinical assessments (resting cardiovascular and anthropometry measures)**		
	Resting blood pressure and heart rate	Blood pressure will be measured using a validated automated sphygmomanometer. Participants will be seated and rested for at least 10 minutes before the blood pressure assessment [38]. Participants will place their forearm on a table with the elbow at an approximate 90° angle, and the cuff will be placed on the upper arm according to the manufacturer’s instructions. Three separate measurements will be taken on both right and left arms, with the average of the 3 measurements used in subsequent analyses.
	Waist circumference, height, weight, and BMI	Weight will be measured using a digital scale (SECA 813 model) with the participant unfasted, barefoot, and dressed in light clothing. Height will be measured barefoot using a wall-mounted stadiometer (SECA 216 stadiometer). Waist circumference will be measured according to the International Diabetes Federation guidelines [39].
	Handgrip strength	Handgrip strength will be measured using a manual dynamometer.
	Functional fitness	Functional fitness will be assessed using the submaximal 6-minute walk test [40]. The participant will be instructed to cover as much distance walking on flat ground in a laboratory setting until they have completed 6 minutes or they choose to stop walking. Risk of falls will be minimized by the AEP^a^ or RA^b^ following the participant closely to enable spotting and assistance should they lose balance. They will also monitor the participant throughout the test for safety (including heart rate and RPE^c^).
	Lower extremity function and mobility	Lower extremity function and mobility will be measured using the Short Physical Performance Battery [41], which involves timing the duration of 5 sit-to-stand repetitions from a chair, feet together, semitandem and full tandem stance, and a 2.44-m walk.
	Balance	Balance will be evaluated using the single-leg balance test. The participant will be instructed to stand on 1 foot for as long as possible without assistance up to a maximum of 60 seconds. To minimize the risk of falls, they will be supported by an AEP or RA, and there will be a wall or sturdy chair in front of them that they can hold onto if needed.

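### Health outcome assessors are declared blinded, but the staffing text gives assessment tasks to roles that also run the program sessions, so the claim is contradicted as written for the 12-week comparison

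*Protocol article*

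**What the plan says.** All references are to the protocol article.

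**Blinding.** The Health Outcomes section makes two statements. The first is "The RA completing assessments will be blinded to the condition (intervention or waitlist control groups". The second concerns the outcome measures, which "will be completed by an RA and a member of the research team who is blinded to the group allocation". Read together, they cover an RA and one further team member.

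**Physical assessment.** In the Exercise Component section, the paragraph on staff training and exercise monitoring says "The AEP will conduct the clinical assessment and group exercise sessions". Table 1 groups blood pressure, anthropometry, grip strength, the 6-minute walk, the Short Physical Performance Battery and single-leg balance under the heading "Clinical assessments (resting cardiovascular and anthropometry measures". For the balance test, Table 1 says of participants that "they will be supported by an AEP or RA". The walk test has a similar provision.

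**Questionnaires.** The Health Outcomes section says "Participants will be asked questions by an experienced health psychologist and RA who has experience interviewing people with cognitive decline".

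**Delivery.** Under Feasibility and Acceptability, the attendance records are "recorded by the AEP and health psychologist facilitating the sessions". The Exercise Component section has the same two roles trained to deliver the program, and the education section has psychologists deliver it.

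**The concern.** Under Recruitment, the waitlist group has 12 weeks of usual care before starting the program. Until then, anyone who runs sessions or keeps the attendance record knows who was allocated to the intervention. If the same staff measure outcomes at 12 weeks, those measurements are not blinded, whatever the Health Outcomes section says.

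Participants know their own group in a waitlist design, so assessor blinding is a safeguard that readers will rely on. It matters most where the assessor can influence the result: encouragement during the walk, grip and balance tests, the way interview questions are put, and scoring of the Montreal Cognitive Assessment (MoCA). The Statistical Analysis section tests health outcomes one-tailed and reports effect sizes, and the abstract says the findings will inform larger trials. A result labelled as blindly assessed when it was not would carry an unrecognised risk of bias into that planning.

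**Working it through.** No figure in the plan depends on this point, so there is nothing to recompute. The check compares the roles that deliver with the roles that assess.

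1. **Who delivers.** The Intervention overview names AEPs and health or clinical psychologists. Feasibility and Acceptability and the Exercise Component section name the AEP and the health psychologist.
2. **Who assesses physical outcomes.** Health Outcomes says a blinded RA, trained and supervised by an AEP. The Exercise Component section says the AEP, in the same sentence that gives the AEP the exercise sessions. Table 1 has an AEP or an RA alongside the participant in the walk and balance tests.
3. **Who administers questionnaires.** Health Outcomes says an RA and a blinded team member, and later in the same section a health psychologist and an RA. The natural reading is that the blinded team member is the health psychologist. That role also facilitates sessions.
4. **Is the overlap one of role or of person?** For the AEP, a single sentence gives both tasks to one role. For the psychologist, the overlap is of role. The Study Design section lists one health psychologist on the team, while the Intervention overview uses plurals for delivery staff. No sentence says that assessors and deliverers are different people.
5. **When does it matter?** Baseline testing is completed before randomization, so there is no allocation to know. The conflict arises at the 12-week assessment, when one group has attended sessions and the other has not.
6. **Which outcomes?** It affects the secondary health outcomes compared between groups. Consent, retention and session attendance do not depend on a blinded assessor.
7. **How many participants?** Data collection is complete for 18 of the planned 20, which leaves at most 20 − 18 = 2 if recruitment continues.

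The two blinding statements and the two staffing statements can all be true only if separate individuals within each role assessed and delivered, or if the AEP's clinical assessment is something other than the outcome assessment. The article states neither.

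**The case against.** The best case for the plan has four parts.

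First, the AEP sentence sits in a paragraph about monitoring during exercise sessions, so the clinical assessment may mean an in-session or pre-exercise check. This is possible. Against it, the paragraph already has its own term for monitoring, the sentence lists the assessment separately from the sessions, and Table 1 uses the same term for the outcome measures.

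Second, the second blinding statement covers a team member who is not an RA, so the psychologist who asks the questions may be a blinded one. The education section mentions a clinical psychologist as well, and the health psychologist may train others to give the MoCA. Different individuals are therefore possible. This part stands: a reader might infer that blinding has been shown to fail, and the article does not support that. It shows an unresolved conflict between roles, and nothing in it disproves the RA's own blinding.

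Third, a reader might infer that assessor blinding is all that protects these outcomes. That goes too far. Blood pressure is taken with an automated device, weight with a digital scale, and the computerised cognitive tasks are captured by software. The quality-of-life, pain and mood scales are patient-reported, so the unblinded participant is the rater and a blinded interviewer gives only partial protection.

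Fourth, the primary aims are feasibility and acceptability, and the Discussion already warns that health effects may not reach significance in so small a sample. This lowers the severity but does not remove the contradiction.

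**Conclusion.** The point holds in a limited form. As written, the article declares the outcome assessors blinded while giving assessment tasks to roles that run the sessions, and it does not say that different people fill them. The claim is contradicted for the 12-week between-group comparison of secondary health outcomes. It is not contradicted for baseline or for attendance-based feasibility, and it is not disproved for the RA.

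No size can be put on any resulting bias, because the document gives no information on who assessed what or on assessor effects. The conclusion rests on two readings: that the clinical assessment in the Exercise Component section is the one headed so in Table 1, and that the health psychologist who asks the questions may be the one who facilitates sessions. Source records could overturn either.

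It should be fixed, because it concerns a stated property of the trial that will be repeated in the results. It does not invalidate the pilot.

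**What to change.** 1. Reconcile the two blinding statements and the interview statement in Health Outcomes with the AEP sentence in the Exercise Component section, so that each 12-week measure has one named role as assessor.
2. From source records, tabulate who assessed each 12-week outcome for each participant, including who else was present at the walk and balance tests.
3. Report as unblinded every outcome assessed by, or with, staff who delivered sessions or knew the allocation. Limit the blinded-assessor statement to the outcomes for which it was true. If the records show that separate, blinded staff did all the assessments, the statement stands and is documented.
4. For any participants still to be assessed, use an existing RA who neither performs the randomization nor delivers sessions, where one is available. The team includes RAs in the plural, but their number is not given, and one of them randomizes. With 18 participants' data already collected, this step can change little.

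The cost is a review of existing records, a field in the data set and a few sentences of text. The downside is that some outcomes may have to be reported as unblinded.
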